### Recruitment

Study participants are recruited at a German inpatient rehabilitation center (https://www.muehlenbergklinik-holsteinische-schweiz.de). Eligibility is determined prior to the start of rehabilitation either by the referring pension insurance agency or by the rehabilitation center if a mild or moderate mental illness or distress or exhaustion is described in the application documents. A physician from the study center therefore continuously screens the incoming application documents of patients who are assigned to the rehabilitation center by the pension insurance agencies. A member of the study team (psychologist) in the study center informs potential participants in writing about the possibility of participating in the study, specifies the possible start of rehabilitation, and suggests a telephone consultation to the participants. The relaying of this information by telephone is supported by a manual. After receiving verbal information during the telephone conversation, the potential participants sign the consent form and return it to the rehabilitation center within 48 h. The written information and the consent form are provided as Additional files 3 and 4. A website provides supplementary and ongoing information about the study (https://www.vor-kardio.de).

### Allocation

Randomization is performed in a one-to-one ratio. The randomization sequence was generated by the principal investigator (MB) using Stata 16.0. Blocks of different size were combined randomly. Allocation concealment is ensured by sealed, opaque, and consecutively numbered envelopes. The envelopes are opened in the study center for randomization only after participants have given informed consent. The group assignment is documented in the study center in the study list through the identification number.

### Blinding

Participants and providers are not blinded. The data analysis is also not blinded.

### Data collection methods

Data are collected via questionnaires, clinical examinations, and the standardized rehabilitation discharge reports. Questionnaires are completed at four measurement points: at the beginning and end of rehabilitation, as well as 3 and 12 months after completion of rehabilitation. The assessments have already been tested during the implementation of the intervention [14] and are described in detail above (Table 2). The 3-month and 12-month follow-up questionnaires are sent from the rehabilitation center. Patients whose follow-up questionnaires have not been received after two weeks are reminded twice at two-week intervals, if necessary. We enclose the questionnaire again with each reminder. Clinical examinations are performed at the beginning and end of rehabilitation. Treatments administered during rehabilitation are documented by the rehabilitation center in the discharge reports at the end of rehabilitation.

### Data management

Data from questionnaires are entered by trained research assistants. We use forms created with Microsoft Access for data entry. When entering the data, the research assistants can only select from a set of valid values. The first 20 questionnaires of each of the four measurement points and subsequently every 20th questionnaire are re-entered by a second independent person. Incorrect completion of questionnaires (e.g., multiple crosses) are logged. Data entries are made immediately when the questionnaires are available to the University of Lübeck. The presence of the questionnaires at the beginning and end of the rehabilitation is documented in the study list of the rehabilitation center. The same applies to the mailing of the 3-month and 12-month follow-up questionnaires. The questionnaires received after 3 and 12 months are documented at the University of Lübeck. The identification numbers of the incoming questionnaires are transmitted by the University of Lübeck to the rehabilitation center. If receipt is confirmed by the University of Lübeck, no reminder is sent. A comprehensive plausibility check is performed for all data prior to our analysis of the data.

### Data monitoring

An external data monitoring committee is not implemented. Short-term and long-term effects are analyzed and published separately. No further interim analyses are planned. No criteria for early study termination have been established.

### Auditing

The status of recruitment, the treatment fidelity, the response rates of the questionnaires, and the number of questionnaires entered are discussed in bi-weekly video conferences between the Universität zu Lübeck and the rehabilitation center.

### Confidentiality

Participants are added to a password-protected study list (Microsoft Excel) with their name, address, and social security number upon consent to participate and are assigned an identification number. This list also documents the treatment group, consent, and the planned start of rehabilitation after randomization. This study list remains at the recruiting rehabilitation center. The rehabilitation center transmits a pseudonymized copy of this list exclusively with the pseudonym, treatment group, date of receipt of consent and planned start of rehabilitation electronically and encrypted to the University of Lübeck at the beginning of each week. The study list will be shredded by the rehabilitation center after all follow-up questionnaires have been sent out. As of that point, the data will be completely anonymized.

The rehabilitation center documents in another list (Microsoft Excel), in which participants are recognized only by their identification number (pseudonymized list), their date of birth, gender, the actual start of rehabilitation and the end of rehabilitation (if necessary, also the early termination of rehabilitation), selected clinical data collected in the rehabilitation center (systolic and diastolic blood pressure, ergometer performance in watts/kg, capacity for last job and other job, recommendations for subsequent services, diagnoses), and the therapeutic services performed during rehabilitation.

The participants’ questionnaires are provided with the identification number in the rehabilitation center and handed over to the study participants by a member of the research team for completion at the beginning and end of the rehabilitation. The participants deliver the questionnaires in an envelope at the reception of the rehabilitation center. Thereafter, these questionnaires are personally handed over to MB by DB every two weeks. The questionnaires of the follow-up assessments after 3 and 12 months, also tagged with the identification number, as well as the reminders, are sent from the rehabilitation center. A stamped return envelope addressed to the University of Lübeck is enclosed with this letter.

Data, pseudonymized with the identification number, are recorded electronically at the University of Lübeck using Microsoft Access. All questionnaires received by the University of Lübeck are stored in locked cabinets at the University of Lübeck and will be shredded in accordance with data protection regulations upon completion of the study on 28.02.2025. Computers at the University of Lübeck that allow access to the data entered are located in locked office rooms and require user authentication in the form of passwords. Accesses can be tracked. Data is stored in folders that are only visible and accessible to the research team at the University of Lübeck. The network in which the computers are integrated is protected against external access and manipulation by a regularly updated firewall system. The University of Lübeck will completely delete the electronically stored questionnaire data 10 years after the end of the study (28.02.2035). To ensure a transparent research process, anonymized data will be permanently stored in a data repository after our primary publication is accepted (https://www.synapse.org).

### Access to data

All authors of the study protocol will have access to the final and fully anonymized data set.

### Statistical methods

We will analyze short-term (end of rehabilitation and 3-month follow-up) and long-term effects (12-month follow-up) using different models and publish the findings separately. We will use mixed models if more than one measurement point needs to be considered, i.e., end of rehabilitation and 3-month follow-up, and generalized linear models otherwise. If baseline scores are available, these will be included as a covariate when estimating the treatment effect. If outcomes are binary, a logit link will be used. High depression, high generalized anxiety, and high cardiac anxiety, as well as age, sex, and education, are tested as possible moderators of the treatment effect on our primary outcome cardiac anxiety assessed at the 12-month follow-up.

For health economic evaluation, we will calculate an incremental cost-effectiveness ratio [44]. Assessments of costs employ a societal perspective [41, 45]. Effectiveness is measured using quality-adjusted life years as derived from the 12-month assessment of the EQ-5D-5 L [28, 30]. The incremental cost-effectiveness ratio is calculated by dividing the difference in costs between both interventions by the difference in effectiveness between both interventions. Bootstrapping is used to compute a 95% confidence interval of the incremental cost-effectiveness [44].

Missing data will be imputed using chained equations [46]. We will create 20 independent data sets with complete values. Parameter estimates of the models will be combined in accordance with Rubin’s rules [47]. Statistical tests will be regarded as significant if the two-sided p-value of a test is less than 0.05. An up-to-date version of Stata (StataCorp, College Station, Texas, USA) will be used to conduct the analyses.

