##### Work ability and job situation

Self-rated work ability is measured using the Work Ability Score [34]. The Work Ability Score is the first item of the Work Ability Index and compares the current work ability with the lifetime best. The scale ranges from 0 („completely unable to work“) to 10 („work ability at its best”). The Work Ability Score correlates strongly with the total Work Ability Index score [35]. We also assess employment, sick leave status and cumulative sickness absence in the last 3 or 12 months (weeks). At the 3-month and 12-month follow-up, we ask when the participants were first working for at least four weeks without absenteeism (time to sustainable return-to-work) [36], and we assess if patients receive a disability pension. The physician’s assessment of work capacity for the last job and the general labor market at the end of rehabilitation are extracted from the standardized medical discharge reports [37].

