**Secondary outcomes**			
Fear	Subscale of the German 17-item version of the CAQ [16]	Continuously, 0 to 4 points	T0, T1, T2, T3
Avoidance	Subscale of the German 17-item version of the CAQ [16]	Continuously, 0 to 4 points	T0, T1, T2, T3
Attention	Subscale of the German 17-item version of the CAQ [16]	Continuously, 0 to 4 points	T0, T1, T2, T3
Change in score for cardiac anxiety	Total score of the German 17-item version of the CAQ [16]	Continuously, − 4 to 4 points	T1, T2, T3
Decrease in cardiac anxiety by 0.2 points	Total score of the German 17-item version of the CAQ [16]	Binary, yes/no	T1, T2, T3
Depression	PHQ-D [25]	Continuously, 0 to 27 points	T0, T1, T2, T3
Generalized anxiety	PHQ-D [25]	Continuously, 0 to 21 points	T0, T1, T2, T3
Somatization	PHQ-D [25]	Continuously, 0 to 30 points	T0, T1, T2, T3
Functional capacity	IRES-24 [26]	Continuously, 0 to 10 points	T0, T1, T2, T3
Blood pressure	Clinical examination	Continuously, systolic/diastolic in mmHg	T0, T1
Endurance	Clinical examination	Continuously, ergometer performance in watts/kg	T0, T1
General health	Visual analog scale of the EQ-5D [27]	Continuously, 0 to 100 points	T0, T1, T2, T3
Health-related quality of life	EQ-5D [28]	Continuously, health state of 11111 corresponds to a value of 1	T0, T1, T2, T3
Motivation to change lifestyle	OutCaRe [31]	Binary, certainly or rather yes vs. uncertain or less	T0, T1
Weekly physical activity	BSA-F [33]	Continuously, minutes	T0, T1, T2, T3
Self-efficacy to exercise	ESES [32]	Continuously, 10 to 40 points	T0, T1, T2, T3
Smoking status	Own development	Binary, yes/no	T0, T1, T2, T3
Weight	Clinical examination	Continuously, body mass index in kg/m²	T0, T1, T2, T3
Self-rated work ability	Work Ability Score [34]	Continuously, 0 to 10 points	T0, T1, T2, T3
Sickness absence	Own development	Binary, yes/no	T0, T2, T3
Sickness absence duration	Own development	Continuously, cumulative sickness absence in the last 3 or 12 months in weeks	T0, T2, T3
Stable return to work	[36]	Binary, yes/no	T2, T3
Time to stable return to work	[36]	Continuously, weeks	T2, T3
Employment	Own development	Binary, yes/no	T0, T2, T3
Disability pension	Own development	Binary, yes/no	T0, T2, T3
Capacity for last job	Medical assessment, standardized medical discharge report [37]	Binary, at least six hours per day or less than six hours per day	T1
Capacity for other job	Medical assessment, standardized medical discharge report [37]	Binary, at least six hours per day or less than six hours per day	T1

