### Sample size

As a minimum important difference for the 12-month follow-up, we defined 0.2 points of the total cardiac anxiety score (0 to 4 points [15, 16]). Although 0.2 points represent only 5% of the scale range, we consider this small gain to be relevant because we are comparing two comprehensive rehabilitation programs. Assuming a standard deviation of 0.6 points [43], 0.2 points correspond to a standardized mean difference of 0.33. To detect this difference with a two-sided error of 5% and a power of 80%, 286 participants are required. Further assuming a response rate of 70% in the 12-month follow-up, we plan to recruit 410 participants (intervention group: n = 205; control group: n = 205) to be able to detect the minimal important difference also in a complete-case analysis. For our primary intention-to-treat analysis with multiple imputation of missing follow-up scores, a difference of 0.2 points is detected with a power of about 92%.

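### Stable return to work and physician-rated work capacity have no baseline score, so the covariate rule leaves them unadjusted although related work variables are collected at T0

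*Protocol article*

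**What the plan says.** The Statistical methods section of the protocol article ties adjustment to the existence of a baseline score: "If baseline scores are available, these will be included as a covariate when estimating the treatment effect". For binary outcomes it adds: "If outcomes are binary, a logit link will be used". It names no other covariate for the treatment effect. High depression, high generalized anxiety, high cardiac anxiety, age, sex and education appear only as possible moderators for the primary outcome.

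Table 2 then decides which outcomes the rule reaches:

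- Stable return to work (yes/no) is listed at T2 and T3.
- Capacity for the last job and capacity for another job come from the discharge report and are listed at T1. Each is scaled as "Binary, at least six hours per day or less than six hours per day".
- The Work Ability Score, sickness absence (yes/no) and employment (yes/no) all have a T0 entry. The section on work ability and job situation says: "Self-rated work ability is measured using the Work Ability Score".
- The responder outcome, "Decrease in cardiac anxiety by 0.2 points", is listed at T1 to T3. Its source is the CAQ total score, which is collected at T0.

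**The concern.** The rule makes adjustment depend on whether an outcome has a baseline score, not on whether useful baseline information exists. Return to work and physician-rated capacity cannot have a T0 value in the form listed, so they fall outside it, while variables on the patient's work situation at T0 are already in the data set. In logistic regression, leaving out a prognostic covariate lowers the power of the treatment test.

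Two features make this worth settling in advance. The Study setting section describes the insurers' rehabilitation as aimed at keeping people in work, so these outcomes will be read closely. In addition, the analysis is not blinded (Blinding) and short-term results are published separately from the 12-month results (Statistical methods). Covariates added later for 12-month return to work could then be chosen with allocation and earlier results by arm already known.

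**Working it through.** **1. The plan's own figures.** The Sample size section states: "Assuming a standard deviation of 0.6 points [43], 0.2 points correspond to a standardized mean difference of 0.33", and "To detect this difference with a two-sided error of 5% and a power of 80%, 286 participants are required".

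- Normal approximation: n per arm = 2 × (1.96 + 0.8416)² × 0.6² / 0.2² = 2 × 7.849 × 9 = 141.3, so 142 per arm (284). The t-test version gives 142.2, so 143 per arm, which is the stated 286.
- Recruitment: 286 / 0.70 = 408.6, so 409 against the stated 410.
- Power with 205 per arm: 0.2 / (0.6 × √(2/205)) = 3.375, and Φ(3.375 − 1.96) = 0.92, as stated.

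These figures concern the primary outcome only. They reproduce, and this point does not change them. The article gives no power for the work outcomes.

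**2. Which outcomes the rule misses.**

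| Outcome | T0 entry in Table 2 | Covariate under the rule |
|---|---|---|
| Work Ability Score, sickness absence and its duration, employment, disability pension | yes | yes |
| 0.2-point decrease in CAQ | source score at T0 | yes, read plainly |
| Stable return to work | no | none named |
| Capacity for last job, for other job | no | none named |

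**3. What a T0 covariate would add.** Taken from the documents: 1:1 allocation, a logit link, two-sided 5% tests ("Statistical tests will be regarded as significant if the two-sided p-value of a test is less than 0.05"), and 286 (complete cases) or 410 (all recruited) participants. Assumed, because the documents give no values: outcome rates of 60% and 73%, and one standard normal T0 predictor x with an odds ratio per SD of 1.5, 2, 3 or 5.

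Model: logit P(Y = 1) = a + δ × arm + ln(OR) × x, with a and δ solved so that the rates in the two arms are 60% and 73%. The odds ratio without the covariate is then (0.73/0.27) / (0.60/0.40) = 1.80. Each of 2,000 simulated trials per setting was analysed with and without x. The Monte Carlo error is √(0.65 × 0.35 / 2000), about 1 point.

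| OR per SD | N=286 without | with | gain (points) | N=410 without | with | gain (points) |
|---|---|---|---|---|---|---|
| 1.5 | 65.1% | 66.4% | 1.3 | 81.2% | 82.1% | 0.9 |
| 2 | 64.8% | 67.9% | 3.1 | 78.5% | 82.7% | 4.3 |
| 3 | 64.2% | 72.4% | 8.2 | 80.2% | 87.4% | 7.2 |
| 5 | 64.7% | 78.0% | 13.3 | 80.4% | 92.7% | 12.3 |

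Gains are taken before rounding. With no treatment effect, the rejection rate in these settings lay between 4.0% and 5.7%, with or without the covariate.

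Return to work depends on returned questionnaires, so N=286 is its complete-case setting. Physician-rated capacity comes from the discharge report, to which the 70% questionnaire response does not apply, so the N=410 columns are nearer for it.

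**4. Effect on the estimate.** At N=286 the adjusted odds ratio averaged 1.86, 1.92, 2.07 and 2.35 for the four predictor strengths, against about 1.81 unadjusted. This is the usual difference between a conditional and a marginal odds ratio, not a correction of bias.

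**The case against.** The strongest reply is that nothing here is an error. An unadjusted comparison of a secondary outcome in a randomised trial is valid, and covariate lists for single secondary outcomes are commonly left to an analysis plan, which is not shown. The rule also says neither *own* nor *only*; that it excludes other covariates is an inference. Most work outcomes in Table 2 do have a T0 value and are adjusted already. Finally, adjustment changes the logit estimand.

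Most of this stands, and it limits the weight of the point. What remains is that the article does fix a rule, and that rule gives these three outcomes no covariate. A better rule needs only data already collected.

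Three stronger readings are tempting but not supported:

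- *The 0.2-point responder is tested unadjusted.* It cannot be computed without the T0 CAQ total, so a baseline score is available and the rule brings it in. Only a strained reading, which asks for a T0 value of the binary variable itself, leaves it out. Under that reading, simulation with SD 0.6, a true difference of 0.2, an assumed control-arm fall of 0.1 and assumed T0–follow-up correlations of 0.3, 0.5 and 0.7 gives power at N=286 of 48%, 62% and 81% without T0 CAQ, and 59%, 69% and 85% with it.
- *Chance imbalance invalidates the unadjusted comparisons, because the Allocation section names no stratification factor.* Randomisation protects the test, and its error rate already allows for chance imbalance, as the null simulations show.
- *The T0 work variables are strong predictors.* The documents report no association with these outcomes. At an odds ratio of 1.5 per SD the gain is about 1 point.

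**Conclusion.** The point holds as a matter of efficiency and pre-specification on secondary outcomes. On the natural reading of the Statistical methods section, stable return to work and the two physician-rated capacity outcomes are compared without covariates, although three related work variables are available at T0 in both arms. The cost is about 1 to 13 percentage points of power. This rests on assumed rates of 60% and 73%, a single predictor, and odds ratios of 1.5 to 5 per SD; where the trial falls in that range cannot be told from the documents. Validity is not in question. The importance is modest, but the remedy is cheap.

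**What to change.** Extend the covariate sentence in Statistical methods along these lines: outcomes without a T0 value that concern work (stable return to work, capacity for the last job, capacity for another job) are adjusted for T0 Work Ability Score, T0 sickness absence (yes/no) and T0 employment (yes/no); the 0.2-point decrease in cardiac anxiety is adjusted for the continuous T0 CAQ total. The second clause only confirms what the rule already implies.

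Because the adjusted odds ratio is conditional on the covariates, report beside it the standardised risk difference: the mean predicted probability with all participants set to one arm, minus the mean with all set to the other.

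The cost is one sentence and one further summary per outcome, with no new data. The T0 questionnaire follows randomisation in Table 3, so these covariates are recorded after allocation; the existing rule already relies on T0 scores in the same way. The wording should be fixed before any results by arm are examined.

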##### Health-related costs

For our health economic evaluation, we use the Questionnaire for Health-Related Resource Use in an Elderly Population [40]. The questionnaire assesses, among others, the type of health insurance, medications taken in the last seven days, outpatient physician visits and therapeutic services used in the last 3 months, as well as rehabilitation measures, outpatient surgery and treatments in outpatient or inpatient hospitals in the last 12 months. The health-related costs are calculated using the rates proposed by Bock et al. [41].

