Treatments during the rehabilitation program	Standardized medical discharge report [37], coding according to the classification of therapeutic services report [39]	Continuously, minutes or hours	T1
Content of the cognitive-behavioral rehabilitation program	[14]	Continuously, 0 to 12 points	T1
Consistency of the approach	[14]	Continuously, 0 to 16 points	T1
Gain in competence	[14]	Continuously, 0 to 40 points	T1
Recommendations for subsequent services	Standardized medical discharge report [37]	Binary, yes/no for 12 subsequent services	T1
Utilization of medical and non-medical services	FIMA [40]	Continuously, resource usage in euro	T3
Diagnoses	Standardized medical discharge report [37], clinical interview[42]	Nominal	T1
Sociodemographic data	Own development	Various (native language, number of children, level of school education, vocational qualification)	T0

*BSA-F* Physical Activity, Exercise, and Sport Questionnaire (German: Bewegungs- und Sportaktivität Fragebogen), *CAQ* Cardiac Anxiety Questionnaire, *ESES* Exercise Self-Efficacy Scale, *EQ-5D* European Quality of Life 5 Dimensions, *FIMA* Questionnaire for Health-Related Resource Use in an Elderly Population (German: Fragebogen zur Erhebung von Gesundheitsleistungen im Alter), *IRES-24* Indicators of rehabilitation status (German: Indikatoren des Reha-Status), *OutCaRe* Outcome of Cardiac Rehabilitation, *PHQ-D* Patient Health Questionnaire, *T0* Beginning of the rehabilitation, *T1* End of the rehabilitation, *T2* 3-month follow-up, *T3* 12-month follow-up

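### QALYs are to be derived from the 12-month EQ-5D-5L score alone, although the index is collected at four time points; the result is close to a true QALY only if the effect is roughly constant over the year.

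*Protocol article*

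**What the plan says.** The health economic paragraph of Statistical methods gives the effect side of the incremental cost-effectiveness ratio (ICER): "Effectiveness is measured using quality-adjusted life years as derived from the 12-month assessment of the EQ-5D-5 L". The ICER is obtained by "dividing the difference in costs between both interventions by the difference in effectiveness between both interventions", and "Bootstrapping is used to compute a 95% confidence interval of the incremental cost-effectiveness".

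Elsewhere in the article, 12-month denotes T3, one occasion 12 months after rehabilitation ends. Data collection methods says: "Questionnaires are completed at four measurement points: at the beginning and end of rehabilitation", followed by 3 and 12 months after completion. The Table 2 row "Health-related quality of life" is the EQ-5D index ("health state of 11111 corresponds to a value of 1"), and its time column lists T0, T1, T2 and T3.

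On the cost side, the Table 2 row "Utilization of medical and non-medical services" is scheduled at T3 only. Health-related costs gives look-back windows that differ by item: seven days for medication, a shorter window for "outpatient physician visits and therapeutic services used in the last 3 months", and 12 months for rehabilitation, outpatient surgery and hospital treatment.

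**The concern.** A QALY is utility accumulated over time. A utility observed on one occasion has no time dimension and has to be given one by assumption. If the T3 difference is taken to stand for the whole year, the differences observed at T1 and T2 count for nothing, although they are measured. An early benefit that fades is then scored as no benefit, and a late benefit is scored as if it had been present throughout.

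This matters because the quantity is the denominator of a ratio. If the between-arm difference at T3 is at or near zero, the ICER is undefined or erratic and its bootstrap interval is unstable, even where patients gained health earlier in the year. The Discussion says the trial is meant to inform pension insurers about wider implementation, so the ICER may bear on that decision.

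**Working it through.** The article states no QALY or ICER figure, so there is nothing of the plan's own to reproduce. The check compares the two ways of forming the effect term.

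**Inputs from the article.** Rehabilitation lasts 4 weeks; follow-ups are 3 and 12 months after its end. In years: T0 = 0, T1 = 4/52 = 0.077, T2 = 0.077 + 0.25 = 0.327, T3 = 0.077 + 1 = 1.077 (56 weeks).

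**Trapezoid weights on the between-arm utility differences:**
- T0: (T1 − T0)/2 = 0.038
- T1: (T2 − T0)/2 = 0.163
- T2: (T3 − T1)/2 = 0.500
- T3: (T3 − T2)/2 = 0.375
- Sum: 1.077

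The share of T3 is 0.375/1.077 = 35%, and that of T2 is 0.500/1.077 = 46%. Counting from T1 only, the weights are 0.125, 0.500 and 0.375, so T3 carries 37.5%. Using T3 alone gives it 100%.

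**Assumptions.** The article gives neither utility differences nor a multiplier for the T3 score. The differences below are illustrative, and the T3 score is multiplied by one year.

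| Assumed difference at T0, T1, T2, T3 | Area under the curve (QALY) | T3 × 1 year |
|---|---|---|
| 0, 0.05, 0.05, 0 (fades) | 0.05 × 0.163 + 0.05 × 0.500 = 0.033 | 0 |
| 0, 0, 0, 0.03 (late only) | 0.03 × 0.375 = 0.011 | 0.030 |
| 0, 0.02, 0.03, 0.05 (grows) | 0.02 × 0.163 + 0.03 × 0.500 + 0.05 × 0.375 = 0.037 | 0.050 |
| 0, 0.05, 0.05, 0.05 (sustained) | 0.05 × (0.163 + 0.500 + 0.375) = 0.052 | 0.050 |

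In the first row the ICER denominator is zero. In the second, T3 alone overstates the gain by 1/0.375 = 2.7 times. In the fourth the two agree closely.

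**Period of the costs.** T3 lies 12 months after T1, so a 12-month look-back from T3 reaches back only to the end of rehabilitation. The four weeks of the index programme, whose added components distinguish the arms, lie before it. The treatments each participant received are, however, extracted from the discharge reports in minutes or hours (Dose delivered; Table 2).

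**The case against.** **The wording could be looser than it looks.** The phrase might mean assessment over 12 months, and a fuller analysis plan may define an area under the curve. That is possible. But the article does not leave the source open: it names one assessment, uses 12-month for T3 elsewhere, and nowhere brings T1 or T2 utilities into the economic evaluation.

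**The effect may be stable.** If so, little is lost, as the sustained case shows. The Background does not settle the shape: for musculoskeletal programmes it reports short- and medium-term gains in depressive symptoms, but also some long-term benefits. A reader should not infer that the effect term will be zero. That needs complete fading of the between-arm difference by T3.

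**Baseline utility.** A reader might infer that it is ignored. The text does not support this. The same section has a general rule that available baseline scores enter as covariates, and EQ-5D has a T0 score. The rule may already reach the QALY comparison, though it would not bring in T1 or T2.

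**Costs.** A reader might also infer that the cost difference omits the programme or most outpatient use. The article does not say that the T3 questionnaire is the only cost source, and it states no scaling rule for the short windows either way. In a condensed article, silence on these details is not an error. What stands is narrower: that questionnaire's longest window cannot contain the index rehabilitation, so its cost has to come from elsewhere.

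**Conclusion.** The point holds for the QALY definition. As written, the effect term uses T3 alone, which under the trapezoid rule should carry about 35% of the weight, and gives nothing to T2, which should carry about 46%. These shares follow from the article's own schedule. The error in QALYs depends on the unknown course of the effect: in the illustrations it runs from almost none (0.050 against 0.052, sustained) to a 2.7-fold overstatement (late only) or total loss of a 0.033 gain (complete fading). Those figures rest on the assumed utility differences and the one-year multiplier.

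Only the secondary health economic evaluation is affected. The primary outcome, its analysis and the sample size are untouched. The change is worth making because it is cheap and, if settled before the T3 data are analysed, removes a choice that could otherwise follow the results.

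**What to change.** Replace the sentence on effectiveness by: *QALYs are the area under the EQ-5D-5L index curve over T0, T1, T2 and T3 (trapezoid rule), with the between-arm difference adjusted for T0 utility.* The adjustment makes explicit what the general covariate rule may already intend.

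State that costs cover the same period and include the index rehabilitation, costed per participant from the treatment data already extracted from the discharge reports.

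The cost is a little more analysis work: the area calculation and unit costs for the programme components. Missing utilities can go through the multiple imputation already planned. No new data collection is needed. Adding resource-use items at T2 is not recommended: recruitment is under way, so only some participants would have them, and with 3-month windows at T2 and T3 the months from 3 to 9 would remain uncovered. If the change counts as a substantial modification, the Trial design section requires Ethics Committee approval and documentation in the register.
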